## Methods/design

### Aims

Specific aims in phase 1 of the study are:

1. To measure the incidence and natural history (onset, severity, and duration) of maternal health problems, in particular urinary incontinence, anal incontinence, perineal pain, sexual health issues, and depression among women having their first child.

2. To explore the contribution of obstetric risk factors; in particular obstructed labour, method of birth, and degree of perineal trauma, to postpartum health problems, taking into account early pregnancy health status.

3. To investigate reasons for non-disclosure of maternal health problems, and for the limited use of primary and specialist health services for specific postpartum health issues.

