### Study hypotheses

Pre-specified study hypotheses are:

1. That vaginal birth assisted by forceps or vacuum extraction is an independent risk factor for incident cases of urinary incontinence, anal incontinence, persisting perineal pain and sexual problems after birth.

2. That both mediolateral episiotomy and midline episiotomy are independent risk factors for incident cases of urinary incontinence, anal incontinence, persisting perineal pain and sexual problems after spontaneous vaginal birth.

3. That mediating factors for urinary incontinence, anal incontinence, persisting perineal pain and sexual problems after spontaneous and assisted vaginal births include fetal size (≥ 4000 grams), maternal size (≤ 150 cm, BMI ≥ 30), length of labour, partogram evidence of obstructed labour, lithotomy position or upright position of the mother during late labour and birth, and non-suturing of perineal tears.

4. That these mediating factors will differ in their strength of association with urinary incontinence, anal incontinence, persisting perineal pain and sexual problems leading to new hypotheses about causal pathways.

5. That the number and severity of physical health problems in the year after birth will increase the probability of women becoming depressed or remaining depressed.

6. That socio-economic factors such as low income, single marital status and non-English speaking background will increase the probability of women becoming depressed or remaining depressed, taking obstetric history into account.

7. That women who have not disclosed health problems to their GP or specialist obstetrician will be willing to discuss the reasons for non-disclosure in a telephone interview.

8. That the reasons for non-disclosure will include: the perception that the problem is 'natural', to be expected after childbirth, too embarrassing to discuss, not a medical problem, or that nothing can be done about it; fear of medical tests and investigations; fear of surgery; fear that treatment might make it worse; fear that treatment might create new problems; fear that the problem will not be regarded as a significant health issue by health professionals.

9. That socio-economic factors such as low income, single marital status, and non-English speaking background will decrease the probability of women experiencing physical and emotional health problems disclosing these health problems to primary and specialist health professionals.

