### Data analysis plan

For aim 1 (incidence, severity and duration of maternal health problems):

▪descriptive frequencies and 95% confidence intervals will be calculated for outcomes of interest at baseline and each follow-up, with stratification to determine the extent of clustering of morbidities and to control for timing of onset of symptoms (prior to pregnancy, during pregnancy, after the birth).

For aim 2 (contribution of pregnancy and birth events to subsequent morbidity):

▪proportions of women reporting outcomes of interest by method of birth (spontaneous vaginal births, forceps assisted vaginal births, vacuum extraction, elective caesarean section, emergency caesarean section) and other obstetric risk factors, including: prolonged first stage labour, fetal position during labour, evidence of obstructed labour in second stage; duration of pushing; fetal presentation at delivery, maternal birth position; use of epidural, spinal or general anaesthesia; degree of perineal trauma; infant birthweight; head circumference; gestation at delivery.

▪multivariable analysis will be undertaken to assess the extent to which method of birth makes an independent contribution to each outcome variable, and to combined morbidity (eg. combined faecal and urinary incontinence). Covariates will include significant labour and birth events, timing of onset of symptoms (pre-pregnancy/during pregnancy/post birth), maternal age and maternal height and early pregnancy BMI. A series of stratified and logistic regression analyses will be performed to validate model choices against stratified data. Generalised linear mixed modelling to take account of repeated measures will be used to determine the effect over time on the associations between health outcomes and covariates.

For aim 3 (reasons for non-disclosure of morbidity to health professionals): descriptive frequencies for prevalent cases will be reported for formal and informal help-seeking and treatment, and for non-disclosure at baseline and each follow-up. Analysis will take into account socio-economic background, the severity and duration of maternal health problems, general health status (SF-36) and extent of co-morbidity.

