Figure 2 provides a schematic overview of key covariates that will be considered in analysis. The arrows represent possible causal associations between covariates based on available epidemiological evidence regarding obstetric risk factors for maternal morbidity. Planning analyses using causal acyclic diagrams has been advocated by Greenland and others as a useful strategy for identifying variables that may mediate or moderate the relationship between an exposure of main interest and primary health outcome/s [55,56]. Figure 2 illustrates the complexity of possible causal pathways and relationships between obstetric risk factors for maternal morbidity. Considering our hypothesis that vaginal birth assisted by forceps or vacuum extraction is an 'independent' risk factor for urinary incontinence, the diagram illustrates the multiple covariates and combinations of covariates preceding the delivery and subsequent to delivery that may mediate the relationship between the mode of birth and the outcome of urinary incontinence. To take one example, the estimated size of the fetus as large for gestational age might lead directly to the decision to conduct an elective caesarean section, or alternatively, via a range of possible pathways to obstruction in second stage labour and a vaginal birth assisted by forceps or vacuum extraction or an emergency caesarean section. A number of other factors may influence the outcome, including the position of the fetus in second stage labour, length of time in active second stage, whether or not an episiotomy is cut and the extent of other genital tract trauma. The conventional statistical approach – used by many researchers – of adjusting for those covariates such as infant size for which data are available is likely to lead to erroneous conclusions. This is not only because data are rarely available for the full range of covariates illustrated in Figure 2, but also because such analyses fail to consider the complex range of possible pathways involved. Simple adjustment for fetal size assumes that the impact will be the same irrespective of other aspects of labour and birth. Biologically this seems somewhat implausible given the extra pressure on the pelvic floor associated with a long labour and large baby often in occipito-posterior position. While these other factors can also be adjusted for in analysis, it may be more useful to conduct separate analyses restricted to women who do and do not experience labour. This is likely to yield less biased estimates of effect for specific causal pathways [57]. The timing of onset of symptoms (and symptom resolution) presents further challenges in analysis. Separate stratified analyses will be performed for incident and prevalent cases of morbidity.

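### Aim 2 model: as written, the onset-timing covariate has a post-birth level that only the outcome can assign, so a pooled fit carries no information on incident morbidity

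*Protocol article*

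**What the plan says.** Four places in the protocol article bear on this point.

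- **Study hypotheses.** Hypothesis 1 is that forceps or vacuum birth "is an independent risk factor for incident cases of urinary incontinence, anal incontinence, persisting perineal pain and sexual problems after birth". Hypothesis 2 makes the same kind of claim for episiotomy after spontaneous vaginal birth. Both concern new onset.
- **Aims.** Aim 2 explores obstetric risk factors "taking into account early pregnancy health status", which is a baseline quantity.
- **Data analysis plan, aim 2.** The multivariable analysis is to "assess the extent to which method of birth makes an independent contribution to each outcome variable". Besides labour and birth events, its covariates include "timing of onset of symptoms (pre-pregnancy/during pregnancy/post birth), maternal age and maternal height and early pregnancy BMI". The same paragraph adds: "A series of stratified and logistic regression analyses will be performed to validate model choices against stratified data".
- **Analysis considerations.** "Separate stratified analyses will be performed for incident and prevalent cases of morbidity".

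The article names three onset levels. It does not say how a woman who never had the symptom is coded, or whether onset stays in the model when incident cases are analysed separately.

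**The concern.** A time of onset exists only for women who have the symptom. The first two levels are settled before birth and are proper baseline information. The third is not: a woman reaches it by becoming a case after delivery. Adjusting for it conditions on the outcome whose dependence on method of birth is to be estimated.

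Hypotheses 1 and 2 are at stake. A pooled model that holds post-birth onset fixed cannot show whether operative birth or episiotomy causes new symptoms. It would still return a coefficient for method of birth, and that coefficient could be reported as the independent contribution although it describes a different group of women.

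**Working it through.** **Inputs from the article (Table 1 and Sample size).** Urinary incontinence 11% after spontaneous and 18% after operative vaginal birth, ratio 2:1, stated total 930, beta 0.20.

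**Assumptions.** The 11% and 18% are treated as risks among women symptom-free before birth; the article calls them prevalence estimates from a survey of recent mothers. Three further quantities are not in the documents and are varied: share of women with antenatal symptoms (5–40%), persistence of those symptoms after spontaneous birth (30–60%), and odds ratio (OR) for operative birth among those women (1.0–1.5).

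**Step 1. Reproduce the plan's figure.** With r = 0.5 and p̄ = (0.11 + 0.5 × 0.18)/1.5 = 0.1333:

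- n = [1.96√((1 + 1/r)p̄(1 − p̄)) + 0.8416√(p₁q₁ + p₂q₂/r)]² / (p₂ − p₁)² = (1.154 + 0.528)² / 0.0049 ≈ 577.
- With continuity correction, n′ = (n/4)[1 + √(1 + 2(r + 1)/(n·r·|p₂ − p₁|))]² ≈ 619.3, rounded up to 620.
- Total = 620 + 310 = 930, as stated.

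This uses alpha 0.05. The printed alpha of 0.5 would give 324, which is a separate matter.

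**Step 2. The effect to be detected.** Expected counts among 620 and 310 women symptom-free before birth:

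| | New case | Not a case |
|---|---|---|
| Spontaneous | 68.2 | 551.8 |
| Operative | 55.8 | 254.2 |

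OR = (55.8 × 551.8)/(254.2 × 68.2) = 1.78.

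**Step 3. Split the same women by the covariate as written.** The outcome is onset by a given follow-up.

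| Onset level | Spontaneous: cases / non-cases | Operative: cases / non-cases |
|---|---|---|
| Post birth | 68.2 / 0 | 55.8 / 0 |
| Never (no level listed) | 0 / 551.8 | 0 / 254.2 |

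Risk is 100% in both birth groups at the first level and 0% in both at the second. Each level is fitted perfectly by its own intercept, for any value of the method-of-birth coefficient, so neither contributes to it. This is complete separation within these levels, and it follows from the definition, not from any assumed rate. If never-symptomatic women are dropped for want of a level, only the first row remains, and it holds cases alone.

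**Step 4. Add women with antenatal symptoms and fit the pooled model to expected counts.** Across all combinations of assumed share and persistence:

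| Analysis | OR if antenatal-group OR is 1.0 | OR if antenatal-group OR is 1.5 |
|---|---|---|
| Only women symptom-free before birth, onset not a covariate | 1.78 | 1.78 |
| Pooled, adjusted for pre-birth status only | 1.29–1.69 | 1.62–1.75 |
| Pooled, with a separate post-birth level | 1.00 | 1.50 |

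The last row returns the OR assumed for antenatally symptomatic women. The middle row mixes onset with persistence. In a simulation of 200,000 women, adding a birth-by-prior-symptom interaction to that model gave the same OR as restricting to symptom-free women.

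**Step 5. Later waves.** If the outcome is current symptoms at a later follow-up, some women with post-birth onset will have recovered, so that level is no longer all cases. It then informs on persistence after onset, still not on onset.

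**The case against.** The strongest reply is that the article does not rest on one pooled model. Analysis considerations promises separate incident and prevalent analyses, aim 2 speaks of early pregnancy health status, and stratified analyses are to check the regression. A reader might infer that the whole plan adjusts the incident effect away. The documents do not support that: an analysis restricted to women symptom-free before birth keeps the full 1.78. This stands, with one condition. The sentence on separate analyses neither withdraws the covariate nor defines the incident denominator, so the effect survives only if onset forms the stratum and is left out of the model.

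Second, post birth may be shorthand for no onset before birth. That would be a legitimate baseline covariate. The wording does not say so, and the two readings give different models. How never-symptomatic women are coded may well be in a fuller plan, but the three named levels are a stated choice.

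Third, complete separation would probably be noticed at a first wave, and the stratified checks might expose it. That makes an unnoticed error less likely; it does not make the specification right.

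A reader might also extend the point to aim 1, where stratification is meant "to control for timing of onset of symptoms (prior to pregnancy, during pregnancy, after the birth"). That does not follow. Describing cases by when symptoms began leaves incidence calculable: onset after birth supplies the numerator, and women without earlier symptoms supply the denominator.

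**Conclusion.** The point holds for the aim 2 multivariable model as worded. A post-birth onset level is post-exposure and outcome-defined, and in a pooled model it removes all information on new onset, whatever rates are assumed. On Table 1's rates an incident OR of 1.78 would go unseen.

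The size of the resulting error cannot be stated for this study. The fitted value equals the OR among antenatally symptomatic women, which the documents do not give; 1.00 and 1.50 above are illustrations. A reader might infer that the estimate would be driven to the null, but that needs the further assumption that method of birth has no effect on persistence.

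The separate incident analysis limits the harm if it is carried out without the covariate. What must be settled is the conflict between the covariate list and the article's own aim 2, hypotheses and Analysis considerations.

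**What to change.** 1. In the aim 2 covariate list, replace onset timing with symptom status known before birth: none, before pregnancy, or new in pregnancy. Take it from the early-pregnancy questionnaire (Q1) and the 30–32 week interview. Say how symptoms that begin between that interview and the birth are classed.
2. Use post-birth onset only to define incident cases.
3. Test hypotheses 1 and 2 among women symptom-free before birth, and analyse persistence separately in the other two groups.
4. Align the Data analysis plan with aim 2 and with the sentence on separate analyses under Analysis considerations, stating that onset is not also a covariate where it defines the stratum.

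The cost is a change of wording before analysis. Both sources of pre-birth symptom data are already in the schedule, and no new collection is needed.

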### Sample

Recruitment of nulliparous women booking to give birth at five metropolitan public hospitals in Melbourne, Australia commenced in April 2003. Participating hospitals have a mix of high and low risk perinatal services. Two hospitals are tertiary level centres with neonatal intensive care (NICU) facilities.

Eligibility criteria for the cohort are: age ≥18 years; nulliparity; estimated gestation 10–20 weeks of pregnancy (according to date of last menstrual period or ultrasound) at enrolment; sufficient proficiency in English to complete telephone interviews and written questionnaires. Criteria for exclusion after study enrolment are: spontaneous abortion prior to 20 weeks gestation; ectopic pregnancy; termination of pregnancy prior to 20 weeks gestation. Women who experience a multiple pregnancy, a stillbirth or neonatal death or a serious maternal illness (e.g. psychotic illness, severe pre-eclampsia) will not be excluded from participation in the cohort, but may be excluded from some analyses.

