### Sample size

Sample size calculations were conducted using Epi Info Version 5 based on prevalence estimates for primary outcomes derived from a population-based Victorian survey of recent mothers [16]. Table 1 shows power calculations for the study with alpha of 0.5 and beta of 0.20, assuming ratios of:

**Table 1 T1:** Sample size calculations

**Exposure comparison (ratio of unexposed: exposed)**	**Outcome of interest**	**Difference**	**Sample size estimate**	**Total number required***
**Spontaneous vaginal birth:forceps/vacuum extraction (2:1)**	Urinary incontinence Faecal incontinence Sexual problems Perineal pain	11% versus 18% 2.6% versus 8% 24% versus39% 20% versus 53%	930 642 360 168	1200 800 450 210
**Emergency caesarean:forceps/vacuum extraction (1:2)**	Urinary incontinence Faecal incontinence Sexual problems	7% versus 18% 3.9% versus 10.5% 29% versus 39%	371 573 841	950 1500 2200
**Elective caesarean:forceps/vacuum extraction (1:5)**	Urinary incontinence Faecal incontinence Sexual problems	2.4% versus 18% 2.8% versus 10.5% 27% versus 39%	276 763 938	900 2500 3100

* Taking into account the relative frequency of different methods of delivery

• 2:1 (unexposed:exposed) for comparison of spontaneous vaginal births with operative vaginal births;

• 1:2 for comparison of emergency caesarean sections with operative vaginal births; and

• 1:5 for comparison of elective caesarean sections with operative vaginal births.

These ratios were based on routinely collected data for women giving birth in Victoria in 1999. Since the five study hospitals are all public hospitals and nulliparity was an eligibility criterion for the study, the ratios were calculated based on confinements of women admitted as public patients for the birth of their first child.

Using these parameters and allowing for 20% loss to follow-up by 18 months postpartum, we estimated that a sample of 1,900 women would be sufficient to test the hypothesis that primiparous women having an operative vaginal birth have a twofold greater relative risk of developing urinary incontinence, faecal incontinence and sexual problems compared with women having a spontaneous vaginal birth, and to detect a relative risk of 2.0 for urinary incontinence for all exposure comparisons.

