Assessment of the representativeness of the sample in terms of obstetric and social characteristics will be conducted by comparing study participants with routinely collected Victorian Perinatal Data for births at participating hospitals, and all Victorian births, corresponding with the recruitment period. This will provide an estimate of the representativeness of the sample in terms of exposures of main interest (e.g. method of birth), and covariates (e.g. mothers' age, marital status, country of birth, infant birthweight).

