The fact that recruitment to the study has been lower than anticipated means that there is increased potential for selection bias related to our primary outcomes. Detailed information on medical conditions, surgical procedures, and symptoms prior to pregnancy has been collected in the baseline questionnaire. Women who report medical conditions, such as Crohn's disease, ulcerative colitis or chronic renal disease that may predispose women to primary outcomes being assessed in the study will be excluded from analyses assessing obstetric risk factors. We will also compare the prevalence of prior medical conditions and symptoms reported by study participants with data from community prevalence studies with respect to urinary and bowel symptoms as a check for evidence of selection bias.

Exclusion of women first attending for pregnancy care at >20 weeks gestation is expected to have a minor impact on the representativeness of the sample. A population-based study conducted by the Victorian Perinatal Data Collection Unit (VPDCU) in 1998 showed that 81.5% of women have their first antenatal visit in the first trimester, and less than 10% attend for a first visit later than 20 weeks [32]. Exclusion of women with insufficient fluency in English to complete written questionnaires and telephone interviews is likely to have greater impact on the representativeness of the sample as approximately 40% of women giving birth at the two tertiary level hospitals during the study period were born overseas in countries where English is not the first language. The restriction of recruitment to women attending public hospitals is a further limitation, especially as it is plausible that differences in the way that care is managed in the private sector (e.g. greater likelihood that labour will be induced and/or augmented, and a higher proportion of women giving birth by caesarean section) may have an impact on maternal health outcomes. Funding constraints and issues of feasibility prevented us from extending the study to these groups.

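### As written, the representativeness check compares first-time mothers with births not limited to first births, over an offset window, so parity is mixed with participation

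*Protocol article*

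**What the plan says.** In the Protocol article, the Sample section opens the criteria with "Eligibility criteria for the cohort are: age ≥18 years; nulliparity; estimated gestation 10–20 weeks of pregnancy". All recruiting sites are public hospitals.

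The last paragraph of the Data analysis plan compares participants with "routinely collected Victorian Perinatal Data for births at participating hospitals, and all Victorian births, corresponding with the recruitment period". The comparator is limited by place and time only; parity and age are not mentioned. The comparison is to cover "exposures of main interest (e.g. method of birth), and covariates (e.g. mothers' age, marital status, country of birth, infant birthweight", among others.

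The Sample size section also uses routine Victorian birth data, for 1999. There the authors reason from the public hospitals and the nulliparity criterion, and state that "the ratios were calculated based on confinements of women admitted as public patients for the birth of their first child".

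Strengths and limitations of the study says that recruitment below expectation raises the potential for selection bias in the primary outcomes. It adds a second check, of prior conditions and symptoms, against "data from community prevalence studies with respect to urinary and bowel symptoms as a check for evidence of selection bias".

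**The concern.** A representativeness check is interpretable only if the comparator is the population that the sample was meant to represent. Here the sample contains first births only, while the comparator as worded takes in births of every order. Method of birth is the study's main exposure and the first characteristic named for comparison. If its distribution differs between first and later births, the comparison estimates a parity difference plus a participation difference and cannot separate them. The same is plausible for maternal age, marital status and birthweight, although the document gives no figures on these.

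The error can go either way. A cohort with no selection could look unrepresentative, and real over- or under-participation could be offset by the parity difference. This matters because the Abstract reports more than 1500 women recruited against 1,900 planned in the Sample size section, and because aim 1 estimates incidence, which depends directly on who took part.

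There is also a timing mismatch. Women enter at 10–20 weeks, so they give birth months after enrolment, yet the comparator births are tied to the recruitment period.

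**Working it through.** The Data analysis plan gives no figure for this check, so there is none to reproduce. The possible size of the parity effect can be built from the protocol's own ratios and two declared assumptions.

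**Step 1: method of birth among public first births.** The Sample size section gives "2:1 (unexposed:exposed) for comparison of spontaneous vaginal births with operative vaginal births". It also sets the ratio to operative vaginal birth at 1:2 for emergency caesarean and 1:5 for elective caesarean. With operative vaginal birth set to 1, the weights are 2 (spontaneous), 1 (operative vaginal), 0.5 (emergency caesarean) and 0.2 (elective caesarean), which sum to 3.7.

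- Spontaneous vaginal: 2/3.7 = 54.1%
- Operative vaginal: 1/3.7 = 27.0%
- Emergency caesarean: 0.5/3.7 = 13.5%
- Elective caesarean: 0.2/3.7 = 5.4%

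Table 1 gives a cross-check, since its last column scales each sample size by the frequency of the two methods compared. The implied operative vaginal share is (360/450) × 1/3 = 26.7% from the first comparison, (573/1500) × 2/3 = 25.5% from the second and (938/3100) × 5/6 = 25.2% from the third. These agree with 27% to within about two points.

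**Step 2: what an all-parity comparator would show.** Let p be the operative vaginal share in first births, f the share of all births that are first births, and m the operative vaginal share in later births. Then

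- all-parity share = f × p + (1 − f) × m
- gap with no selection = p − all-parity share = (1 − f)(p − m)

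Neither f nor m is in the document. I assume f = 0.35 to 0.45 and m = 0.03 to 0.12, and take p = 0.270.

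| f | m | All-parity share | Gap | Gap in standard errors, n = 1500 |
|---|---|---|---|---|
| 0.35 | 0.03 | 11.4% | 15.6 points | 13.6 |
| 0.35 | 0.12 | 17.3% | 9.8 points | 8.5 |
| 0.45 | 0.03 | 13.8% | 13.2 points | 11.5 |
| 0.45 | 0.12 | 18.8% | 8.3 points | 7.2 |

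The standard error is √(0.27 × 0.73/1500) = 1.15 points, so the 95% half-width is about 2.2 points. If later births had the same 27% rate, the gap would be zero. With the lowest Table 1 value, p = 0.252, the range becomes 0.55 × (0.252 − 0.12) = 7.3 points to 0.65 × (0.252 − 0.03) = 14.4 points.

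**Step 3: masking.** Suppose that participation lowered the operative vaginal share in the cohort by 5 points, from 27% to 22% (an illustrative figure). Against an all-parity share of 11.4–18.8%, the cohort would still appear 3.2 to 10.6 points too high. The sign of the true selection would be reversed.

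**Step 4: the window.** Term is taken as 40 weeks. The earliest term birth is to a woman enrolled at 20 weeks on 1 April 2003: 20 weeks later is 19 August 2003. The latest is to a woman enrolled at 10 weeks on 31 December 2005: 30 weeks later is 29 July 2006. A comparator window of April 2003 to December 2005 therefore includes about four and a half months with no participants' term births and omits up to seven months with them.

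The effect is sharpest for the replacement hospital. According to the section on changes to the protocol, approval to recruit there came in June 2005. The first term births could fall no earlier than 1 June 2005 + 20 weeks = 19 October 2005, about ten weeks before the window closes.

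**The case against.** The strongest reply is that the text is silent on parity and does not say that all parities are included. This is a condensed article, and the filter on a data extract is the sort of detail that may sit in a fuller document. The team's other use of routine Victorian data was limited to "confinements of women admitted as public patients for the birth of their first child", so they may well do the same here. That stands against any claim about what the analysis will show. It does not remove the point: the comparators are named, one of them as all births in the state, and the restriction that the authors found necessary in the Sample size section is not carried over.

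A reader might infer more than this, and the document does not support it:

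- *That the check cannot reveal selection bias.* Country of birth is among the characteristics compared. It stays informative, particularly about the English-language requirement, which Strengths and limitations of the study expects to matter more than late booking.
- *That this comparison is the main safeguard.* The step labelled as a check for selection bias is the separate comparison with community prevalence studies. That section states no age or parity matching for it, but this is silence and not an error.
- *That including private patients is a serious flaw.* Recruitment procedures puts private patients at 2.1% of confinements at the study hospitals, so the effect there is negligible. State-wide, including private births serves a purpose, because the authors name the restriction to public hospitals as a limitation.

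Two further objections stand in part. The size in points depends on assumed inputs. The timing phrase could be read as births corresponding to the recruited women, and the document gives no means of estimating how much a shift of some months would change any characteristic.

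**Conclusion.** The point holds as one of specification. Followed as written, the representativeness comparison of method of birth, and plausibly of age, marital status and birthweight, is confounded by parity and can create or hide differences due to participation. For operative vaginal birth the artefact would be about 8–16 points with no selection, against sampling error of about ±2.2 points at n = 1500.

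That size rests on four things: the comparator being taken literally as all parities, the 1999 ratios still applying, first births being 35–45% of all births, and 3–12% of later births being operative vaginal. The last two are assumptions, and the gap vanishes if first and later births have equal rates. The calculation also applies the public-patient rate to all first births, which is close for the study hospitals but only approximate state-wide.

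The window offset is a matter of dates, but its effect on the comparison is unknown and probably secondary to parity. None of this alters a sample size, an error rate or an effect estimate. It affects how far readers can rely on the statement of representativeness.

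**What to change.** In the last paragraph of the Data analysis plan, restrict both comparators (participating hospitals and state-wide) to first births to women aged 18 or over. Define the period as the one in which participants gave birth, about August 2003 to July 2006, in place of the recruitment period. Show the state-wide comparator twice, for public patients and for all first births, so that the difference between public and private care stays visible.

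The cost is a filtered extract of the same perinatal data and a sentence or two of text. The Sample size section shows that first births to public patients can be identified in routine Victorian data. Weighting the aim 1 estimates to the restricted comparator would be an optional sensitivity analysis; the point does not depend on it.
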